**Figure 2 F2:**
[figure not shown]
Conceptual model of the primary aim.

Regarding our primary objective, two kind of analysis will be conducted: Pearson correlation and mediation. We computed an *a priori* power analysis using G^*^Power software to estimate the sample size for these tests. To reach a medium effect size (i.e., r = 0.3), with an α-error of 5% (two-sided) and a β-error of 80%, the total sample size represents 84 participants for Pearson correlations and 149 participants for mediation analysis (based on a three groups IV and one mediator). We decided to recruit 300 youth in our study to allow for up to half of the participants dropping out of the study.

To reach our secondary objective, we will first identify the most powerful predictors between risk and protective factors with linear regression analysis. Then, to assess the weight of each risk and protective factor identified with linear regression in the relation between the difference of HONOSCA-SR scores and WHOQOL-BREF scores between T0 and T1, mediation/moderation analyses will be conducted using the PROCESS macro in SPSS (52).

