At T0, a cognitive functions assessment (including intellectual and executive functions) will be conducted, using the Wechsler Adult Intelligence Scale 4th edition (WAIS-IV) (21), the Test of Attentional Performance version 2.3.1 (TAP 2.3.1) (38), the Stroop Task (39–42), the Tower of London Test (TOL) (43, 44) and the Behavior Rating Inventory of Executive Function—Self-report (BRIEF-SR) (45, 46). An estimate of the participant's intelligence quotient (IQ) will be calculated based on a validated short form of the WAIS-4 (47), including four subtests: vocabulary, similarities, figure weight and matrix reasoning. Participants presenting an IQ estimation below 75 will be excluded from the statistical analysis. Four TAP 2.3.1 subtests will be used to assess alertness, divided attention, flexibility, and working memory. Cognitive inhibition will be assessed by the Stroop task and planning task will be assessed by the TOL. The BRIEF-SR, a 75-item self-report questionnaire, assesses the adolescent's view of his or her cognitive, emotional and behavioral functions. BRIEF-SR consists of two major index subscales and a composite of the two, which are the Behavioral Regulation Index (BRI), the Metacognition Index (MI), and the Global Executive Composite (GEC). BRI comprises inhibit, shift and emotional control scales, while MI comprises initiate, working memory, plan/organize, organization of materials and monitor scales. Higher scores are positively related with lower levels of executive functions. Cognitive insight will be measured by the Beck Cognitive Insight Scale (BCIS) (48, 49), a 15-item self-report questionnaire on a four-point scale (0–3). This instrument contains two sets of items: a nine-item self-reflectiveness subscale and a six-item self-certainty subscale. A composite index is calculated by subtracting the score for the self-certainty scale from the score for the self-reflectiveness scale.

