### Data Analysis and Sample Size

Regarding our conceptual model, earlier illustrated in Figure 2, genetic vulnerability and environmental factors (independent variables), will be, respectively, assessed by self-reported psychiatric family history and both CTQ-28 and FAD-12 questionnaires. Firstly, we expect that youth's psychopathology during the transition period, assessed by YSR/11–18 internalizing and externalizing subscales, GHQ-12, BDI-II, BSS and BIS-11, will play a role as a mediator between previously described independent variables and change in quality of life and mental health care need between T0 and T1 (dependent variables). Thus, these variables over the transition period, evaluated by HONOSCA-SR and WHOQOL-BREF, will allow to define distinct trajectories. Secondly, dimensional aspects will be analyzed as moderating factors, representing protective or risk factors in this process. The evaluated dimensional aspects are intellectual and executive functions (WAIS-IV, TAP 2.3.1, Stroop Task, TOL, BRIEF-SR, BCIS), emotional regulation (ERQ-CA), social adaptation (SASS) and quality of care (HAQ-CP).

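### The sample-size statement gives β as 80%, its mediation figure of 149 does not reproduce from its stated inputs, and the powered model is not the one the analysis section describes

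*Protocol article*

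**What the plan says.** All places are in the protocol article.

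- **Data Analysis and Sample Size, power paragraph (after Figure 2).** The effect size is given as "To reach a medium effect size (i.e., r = 0.3"), the error rates as "with an α-error of 5% (two-sided) and a β-error of 80" per cent, and the tool as G*Power. Two results follow: "the total sample size represents 84 participants for Pearson correlations" and "149 participants for mediation analysis (based on a three groups IV and one mediator"). The target of 300 is justified as allowing up to half the participants to drop out.
- **Same section, opening paragraph.** The model is set out as "genetic vulnerability and environmental factors (independent variables), will be, respectively, assessed by self-reported psychiatric family history" for the genetic part, and the CTQ-28 and FAD-12 for the environmental part. The mediators are YSR internalizing, YSR externalizing, GHQ-12, BDI-II, BSS and BIS-11. The dependent variables are the changes in HONOSCA-SR and WHOQOL-BREF.
- **Secondary Outcomes, Baseline Assessment (T0).** "Participants presenting an IQ estimation below 75 will be excluded from the statistical analysis". No expected rate is given.
- **Study Population.** A previously documented IQ below 75 already bars entry.
- **Attrition Bias.** Retention above 70% is cited for similar populations.

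**The concern.** The power paragraph is the only justification for the size of the study, and it has three faults a reader can check.

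1. β is the probability of missing a true effect. A β of 80% is 20% power, which no one would plan for.
2. The figure of 149 sets the recruitment target. If it does not follow from the inputs printed beside it, nobody can tell what the study is powered to detect.
3. The inputs describe one three-level factor and one mediator, while the paragraph before describes several independent variables and several mediators. The power quoted may therefore not apply to the analysis that will be reported.

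In addition, the dropout allowance is matched to 149 almost exactly, yet a second source of loss, the IQ exclusion after enrolment, is not counted.

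**Working it through.** **Inputs.** From the power paragraph: r = 0.3, two-sided α = 0.05, three-group independent variable (two dummy variables), one mediator, stated N of 84 and 149, recruited N of 300, dropout up to 50%. From Attrition Bias: retention 70%. Assumed, because no rate is given: IQ exclusion of 1%, 2%, 5% or 10%.

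**1. Pearson correlation (the plan's own figure first).** Fisher approximation: N = ((z₀.₉₇₅ + z_power) / atanh r)² + 3, with atanh 0.3 = 0.3095.
- Power 80%: ((1.960 + 0.842) / 0.3095)² + 3 = 84.9, so 85. The exact bivariate-normal calculation gives 84 (power 80.0%). The stated 84 is reproduced.
- Power 20% (β = 80% taken literally): ((1.960 − 0.842) / 0.3095)² + 3 ≈ 16.

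**2. Mediation.** Regression power = P(F′ > F_crit), where F′ is noncentral F with u tested terms, v = N − p − 1 for p predictors, and noncentrality f²N. Here f² = r²/(1 − r²) = 0.09/0.91 = 0.0989. For the joint-significance test, power is taken as the product of the powers of the two paths.

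| Test keeping the three-group variable, 80% power | N needed | Power at 149 |
|---|---|---|
| Two-df test of the group factor (u = p = 2) | 101 | 94% |
| Overall test, two dummies plus mediator (u = p = 3) | 115 | 90% |
| Joint test, a = b = 0.3, no direct effect (b-path f² = 0.09 × 0.91/0.91 = 0.09) | 123 | 89% |
| Joint test, all pairwise correlations 0.3 (partial r = (0.3 − 0.09)/(1 − 0.09) = 0.231; f² = 0.056) | 159 | 77% |

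None gives 149. Matches or near matches need inputs that the text does not state:
- f² = 0.09 (r² used in place of r²/(1 − r²)) with five predictors: N = 149, power 0.803. This is the only exact match found.
- Three predictors at 90% power: N = 148.
- Joint test with a single-df independent variable and all correlations 0.3: N = 151.

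Within the three-group model, the two joint tests give power of 89% and 77% at 150 completers, and 98% and 92% at 210.

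**3. Powered model against described model.**

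| | Power paragraph | Model paragraph |
|---|---|---|
| Independent variables | one, with three groups | family history, CTQ-28, FAD-12 |
| Mediators | one | six scores |

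The three groups may be the in-patients, out-patients and controls named in the Abstract. That is an inference, and the model paragraph does not list group among the independent variables.

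**4. Loss allowance.** 149/(1 − 0.5) = 298, and 300 × 0.5 = 150, so one participant is spare.

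| Assumed IQ exclusion | Left after 50% dropout | Left at 70% retention | Dropout that leaves 149 |
|---|---|---|---|
| 0% | 150 | 210 | 1 − 149/300 = 50.3% |
| 1% | 148.5 | 207.9 | 1 − 149/297 = 49.8% |
| 2% | 147 | 205.8 | 1 − 149/294 = 49.3% |
| 5% | 142.5 | 199.5 | 1 − 149/285 = 47.7% |
| 10% | 135 | 189 | 1 − 149/270 = 44.8% |

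**The case against.** The β figure is plainly a slip: 84 reproduces at 80% power and no number changes. For 149, the article names neither the G*Power routine nor the effect on each path, and an article may leave that detail to the full protocol. The figure lies inside the range of defensible answers, and 115 has no special standing because it comes from an overall regression test, not a test of an indirect effect. Five predictors could even arise from the stated design, as two dummies, the mediator and two group-by-mediator terms. On several readings 149 gives about 90% power.

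Most of this stands. It means 149 cannot be called too small, and no single figure can be put in its place from the article alone. It does not rescue the statement. The article prints a result next to the inputs said to produce it, and the two do not agree under any method tried. The five-predictor route is conjecture, and it also needs r² used as if it were f². Nor can a missing analysis plan explain why adjacent paragraphs describe different models.

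On losses, the objection is right that the IQ exclusion is small beside the allowance. Documented low IQ is screened out at entry, and at the cited 70% retention about 200 participants remain after an assumed 5% exclusion. About 29% would have to be excluded before the number fell to 149 (1 − 149/210 = 0.29).

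**Conclusion.** The point holds in three parts.

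- **β is misstated.** The text means 80% power (β = 20%), and 84 is unaffected.
- **149 is unsupported as stated.** With the three-group variable, r = 0.3 and 80% power, the tests tried give 101 to 159 and never 149. This rests on the regression and joint-significance methods shown. A routine not tried could behave differently, which is why the routine needs naming.
- **The power claim is attached to a model other than the one described.**

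A narrower fourth part concerns losses. The allowance of one half covers dropout alone, with one participant spare. At the full 50% dropout, more than two IQ exclusions take the number below 149. At an assumed 5% exclusion the tolerable dropout is about 48%.

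A reader might infer more than this, and the article does not support it:
- *That the study was planned at 20% power.* The 84 shows otherwise.
- *That 149, and so 300, is too small.* The 149 sits within the computed range.
- *That the IQ exclusion uses up the dropout allowance.* At 5% it takes 15 of about 150.
- *That many separate indirect effects are each tested at 5%, with a large false-positive risk.* The article lists measures in a conceptual model and does not say each combination is tested separately. Multiplicity handling may sit in an analysis plan that is not shown.

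**What to change.** 1. Replace the β phrase with: power of 80% (β = 20%).
2. Restate or recompute the mediation figure for the model in the opening paragraph of Data Analysis and Sample Size. Give the routine, the effect size for each path, the number of predictors and the terms tested. If the three-group variable is intended, name it among the independent variables and say how it relates to family history, CTQ-28 and FAD-12.
3. Report the power of that model at 150 and 210 completers (50% and 70% retention).
4. State that 300 tolerates a combined loss of about 50% from dropout and the IQ exclusion, and give the expected exclusion rate. If the recomputed figure differs from 149, update this tolerance too.

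The cost is a text correction and one recalculation. N = 300 stays and no participants are added. The quoted power may become less favourable once it refers to the fuller model.

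### The sample-size statement gives a β-error of 80% (20% power), but its 84 participants correspond to 80% power

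*Protocol article*

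**What the plan says.** The protocol article, under *Data Analysis and Sample Size*, sizes the study for the two analyses of its primary objective, Pearson correlation and mediation. It reports a "power analysis using G^*^Power software to estimate the sample size for these tests". The inputs and results are:

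- Effect size: "To reach a medium effect size (i.e., r = 0.3".
- Error rates and first result: "with an α-error of 5% (two-sided) and a β-error of 80%, the total sample size represents 84 participants for Pearson correlations".
- Second result: "149 participants for mediation analysis (based on a three groups IV and one mediator".
- Recruitment target: "We decided to recruit 300 youth in our study to allow for up to half of the participants dropping out of the study".

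This is the only place in the article where a power or a type II error rate is given.

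**The concern.** The sentence names the two error rates side by side, α at 5% and β at 80%. β is the type II error rate, and power is 1 − β. Taken at its word, the plan accepts an 80% chance of missing the effect it is sized to detect, which is a power of 20%. No study would be designed that way, and a sample of 84 looks far too large for it.

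The statement justifies the sample size for the primary objective. If the error rate is wrong there, a reader has no correct statement of the study's power anywhere in the article. For the correlation, the intended power can be recovered by recomputing 84. For mediation it cannot, because the article gives no test, degrees of freedom or path coefficients behind 149. The stated β is then all that the reader has.

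**Working it through.** **Inputs**, all from *Data Analysis and Sample Size*: r = 0.3, α = 0.05 two-sided, β stated as 0.80, N = 84 for the correlation. The null value is taken as ρ = 0, which the article does not spell out.

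**Formula (Fisher z).** n = ((z₁₋α/₂ + z_power) / atanh(r))² + 3, with atanh(0.3) = 0.3095 and z₀.₉₇₅ = 1.960.

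**Step 1: reproduce 84, reading 80% as power (β = 20%).**

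- z_power = 0.842, so n = ((1.960 + 0.842) / 0.3095)² + 3 = 84.9, which rounds up to 85.
- Adding the usual bias term r/(2(n − 1)) to atanh(r) gives power 0.8001 at n = 84, so N = 84.
- The exact bivariate-normal model gives power 0.7955 at n = 83 and 0.8003 at n = 84, so N = 84.
- A noncentral t calculation with fixed X gives N = 82.

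All four results lie within 2 of the stated 84, and two of them equal it.

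**Step 2: take the statement literally (β = 80%, power 20%).**

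- z_power = −0.842, so n = ((1.960 − 0.842) / 0.3095)² + 3 = 16.1, which rounds up to 17.
- The exact model gives power 0.194 at n = 15 and 0.206 at n = 16, so N = 16.

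**Step 3: could sidedness explain the gap?** One-sided Fisher z gives 68 at 80% power and 10 at 20% power. Neither is 84, so the two-sided 5% was used as stated.

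| Reading of the statement | N, Fisher z | N, exact model |
|---|---|---|
| β = 80% (power 20%) | 17 | 16 |
| β = 20% (power 80%) | 85 | 84 |
| Stated in the article | 84 | 84 |

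**Step 4: what depends on it.** The target of 300 follows from the mediation figure and the dropout allowance: 149 / (1 − 0.5) = 298. The 149 was not recomputed, because its inputs are not given.

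**Step 5: power if half drop out.** With 150 completers, the Fisher z power for r = 0.3 is Φ(0.3095 × √147 − 1.960) = Φ(1.79) = 0.96. This applies to a single correlation only.

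**The case against.** The strongest reply is that this is a slip of labelling and nothing more. The article calls the calculation a power analysis, 80% is the conventional power, and 84 is reproduced as soon as 80% is read that way. A statistical reader will make the correction unprompted. The wrong label did not enter the computation of 84, and 300 comes from 149 and the dropout allowance. Nothing shows that 149 or 300 is wrong. On any reading consistent with its own numbers, the study is not underpowered for a correlation of 0.3.

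Most of this stands. It limits the consequence, and the point should not be read as a challenge to 84, 149 or 300. It does not make the sentence correct: the text names the β-error explicitly, and no other statement in the article puts it right. The reassurance from recomputing also covers only the correlation, since 149 offers no such check.

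A second objection concerns quoting 96% power at 150 completers. That figure describes the less demanding of the two analyses. Mediation needs 149 of the 150 who would remain after 50% dropout, so 96% quoted without that limit would flatter the design. This is fair. The figure is correct, but it is optional and must be tied to a single correlation.

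**Conclusion.** The statement is wrong as written. A β-error of 80% is a power of 20%, which would need 16 or 17 participants, about one fifth of the 84 given. The 84 matches a power of 80% (β of 20%), with exact power 0.8003. The conclusion assumes a test of ρ = 0 and uses only inputs stated in the article. It holds under each method tried.

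The practical consequence is small: 84 and the recruitment target of 300 are unchanged, and nothing in the conduct of the study is affected. The point still deserves correction, because this is the only power statement and it supports the primary objective. The power behind 149 remains unverified.

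**What to change.** In *Data Analysis and Sample Size*, replace the stated β-error of 80% with *a β-error of 20% (power 80%)*. At the same time, confirm from the saved software output that 149 was also computed at 80% power.

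Optionally, add that 150 completers give about 96% power for a single Pearson correlation of 0.3, and say that this does not describe the mediation analysis.

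The cost is a one-line correction and one look at the saved calculation. If 149 is confirmed at 80% power, no sample size, analysis or procedure changes.

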**Methods and Analysis:**
*Transition_psy* is a multicenter prospective longitudinal cohort study. The transversal and trans-diagnostic approach consists of a dimensional evaluation: 300 youth at the age of 17 will be included in a cohort of in-patients, out-patients and control group. Participants will be assessed at baseline (T0) and 24 months later (T1). The primary objective to determine changes in self-rated Health Of The Nation Outcome Scales For Children And Adolescents (HONOSCA-SR) and WHO Quality of Life-BREF (WHOQOL-BREF) scores between T0 and T1. Pearson correlation and mediation analysis will be performed. A secondary objective analysis using mediation and moderation models with several dimensional aspects, including self-reported and cognitive measures, will be conducted to disentangle the potential relationships between the two scores.

**Discussion:** Transition from CAMHS to AMHS occurs at a crucial age in terms of the continuum between adolescent and adulthood psychopathology. This collaborative and cohesive protocol between CAMHS and AMHS represents the first national cohort study about Transition Psychiatry in French-speaking Belgium.

**Ethics and Dissemination:** The study protocol was approved by the Institutional Review Boards (IRB) of the three participating sites. Results will be published in peer-reviewed journals and disseminated at national and international conferences. This trial was registered in ClinicalTrials.gov (Identifier: NCT04333797) on 3 April 2020.

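### The declared moderation of the path from vulnerability to outcome has no stated analysis: the PROCESS step is attached to the link between the two outcome changes, which does not estimate buffering

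*Protocol article*

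**What the plan says.** All places are in the protocol article.

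- **Data Analysis and Sample Size, opening paragraph (conceptual model).** The independent variables are vulnerability: "genetic vulnerability and environmental factors (independent variables), will be, respectively, assessed by self-reported psychiatric family history and both CTQ-28 and FAD-12 questionnaires". Psychopathology "will play a role as a mediator between previously described independent variables and change in quality of life and mental health care need between T0" (the interval ends at T1), so the two changes are the dependent variables. The moderators follow: "dimensional aspects will be analyzed as moderating factors, representing protective or risk factors in this process". They are intellectual and executive functions, emotional regulation, social adaptation and quality of care.
- **Same section, after Figure 2, primary objective.** "Regarding our primary objective, two kind of analysis will be conducted: Pearson correlation and mediation". Moderation is not listed.
- **Same section, secondary objective.** Linear regression first selects the strongest predictors among the risk and protective factors. The weight of each selected factor is then assessed "in the relation between the difference of HONOSCA-SR scores and WHOQOL-BREF scores between T0 and T1, mediation/moderation analyses will be conducted", with the PROCESS macro in SPSS.
- **Abstract, Methods and Analysis.** The secondary mediation and moderation models are meant "to disentangle the potential relationships between the two scores", which matches the PROCESS step and not the conceptual model.

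**The concern.** The same factors are given two different relations to moderate. In the conceptual model they change how strongly vulnerability leads to psychopathology and then to a worse course. In the analysis text they change how two outcomes, both rated by the participant at T0 and T1, relate to each other.

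Only the first relation corresponds to buffering of risk. It is also the one for which no analysis is stated, because the primary objective stops at correlation and mediation. The Introduction and Discussion look to the study to identify risk and protective factors. If the analysis follows the text as written, the moderation declared in the conceptual model is never tested. A later analysis plan could follow either passage and claim to agree with the protocol.

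**Working it through.** **1. The two definitions side by side**

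| | Conceptual model | PROCESS step and Abstract |
|---|---|---|
| Starting variable | Vulnerability (family history, CTQ-28, FAD-12) | Change in HONOSCA-SR |
| Mediator | Psychopathology (YSR, GHQ-12, BDI-II, BSS, BIS-11) | None named |
| End variable | Change in HONOSCA-SR and in WHOQOL-BREF | Change in WHOQOL-BREF |
| Role of the factor | Moderates the process above | Weighed in the relation between the two changes |

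The direction in the right-hand column is my reading. The article names a relation and gives no equation.

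**2. What each interaction estimates.** Write V for vulnerability, P for psychopathology, W for the factor, and dH and dQ for the changes in HONOSCA-SR and WHOQOL-BREF.

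- Buffering: the V×W coefficient in P ~ V + W + V×W, or the P×W or V×W coefficient in dH (or dQ) ~ V + P + W + P×W + V×W.
- Link between outcomes: the dH×W coefficient in dQ ~ dH + W + dH×W. The relation named in the text has no V or P in it, so this coefficient describes how tightly the two scales co-vary at different levels of W.
- Regression step: as stated, it looks for predictors. A main effect of W is an overall association, and no V×W term is stated.

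**3. The plan's own figures.** It states 84 for correlation, 149 for mediation and 300 recruited, and gives no figure for moderation. With Fisher's z, n = ((1.960 + 0.842)/atanh 0.3)² + 3 = 84.9, so 85 against 84. For mediation, f² = 0.09 with 5 predictors returns 149, but both inputs are assumed because the article does not give them. For dropout, 149/(1 − 0.5) = 298, about 300. None of this is in dispute.

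**4. Illustrative simulation.** n = 150, that is 300 × 0.5; 3,000 runs; two-sided 5% tests. Assumed: standardised V and W, V effect 0.3 in absolute size, residual correlation of dH and dQ −0.5. In case (d), V acts on P (0.3) and P on each change (0.3), with no direct effect of V.

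| Truth | V×W on dH | dH×W on dQ |
|---|---|---|
| (a) W buffers V directly on both changes, 0.3 | about 93% | about 15% |
| (b) W buffers V on care need only, 0.3 | about 93% | about 6% |
| (c) No buffering; W alters the dH–dQ coupling by 0.25 | about 5% | about 89% |
| (d) W buffers the V → P path, 0.3 | about 17% | about 5% |

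Two further results limit what the table can be used for:

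- In (c), suppose W must first pass the regression step (assumed rule: a 5% test on either change). W is then both selected and significant in only about 10% of runs.
- In (d), V×W tested on P itself is significant in about 93% of runs. A test on outcome change that leaves out the mediator would therefore miss most buffering on the first path.

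At n = 300, case (a) gives above 99% against about 25%. A larger sample does not make the two tests equivalent.

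**The case against.** **These may be two separate questions.** Figure 2 is captioned as the model of the primary aim, while the PROCESS step serves the secondary objective and agrees with the Abstract. The link between the two changes may be a deliberate secondary question. That is a fair reading, and it is why this analysis need not be deleted. It does not close the gap: the conceptual model says the factors will be analysed as moderators, and neither objective then has an analysis that does so.

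**Risk and protective factors are not only buffers.** The Introduction also asks how the dimensions affect quality of life and care need, and regression main effects answer part of that. This stands. A reader might infer that the stated analysis misses the risk/protective question altogether; the text does not support that.

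**A factor that only alters how two questionnaires co-vary would be called protective.** A reader might infer this too. It does not follow, because factors reach PROCESS only after selection as predictors. Under the screening rule assumed above, the rate falls from about 89% to about 10%.

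**The absence of a vulnerability term is inferred.** No equation is given, and vulnerability measures might enter the regression or a PROCESS model. That is possible, but the relation named in the text does not include them.

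**Detail belongs in the analysis plan.** Model detail does. The point here is that two stated targets differ, and the article does not reconcile them. Figure 2 is not shown, but the conceptual model is described in words and nothing here rests on the figure.

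**Conclusion.** The mismatch stands on the text alone. The moderation declared in the conceptual model has no stated analysis, and the moderation that is stated concerns the link between two variables that the model treats as outcomes. That link does not estimate whether a factor buffers vulnerability, and the regression step as written does not either.

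The point is limited to the moderation claim. It does not affect the sample size, the correlation or the mediation analysis.

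A reader might turn the simulated contrast (about 93% against 15%) into a loss of power for this trial. The documents do not support that. The figures rest on assumed coefficients, on buffering that acts directly on the outcomes, and on no regression screen; moving the buffering to the path from vulnerability to psychopathology changes them completely. Nor can the stated test be said never to react to buffering: it picks up a weak indirect signal in about 15% to 25% of runs when buffering acts on both outcomes. What holds in every setting is that the two interactions are different estimands. This should be corrected before analysis, as a clarification of the analysis text.

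**What to change.** In Data Analysis and Sample Size, specify the declared moderation as moderated mediation in PROCESS:

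- independent variable: vulnerability (family history, CTQ-28, FAD-12);
- mediator: psychopathology, as already listed;
- moderator: the factor, acting on the path from vulnerability to psychopathology, the path from psychopathology to change, or both, and on the direct path;
- dependent variable: each outcome change in turn.

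Keep the mediator. Testing vulnerability × factor on outcome change alone would miss much of any buffering on the first path.

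Keep moderation of the relation between the HONOSCA-SR and WHOQOL-BREF changes as a separate, descriptive secondary analysis that supports no buffering claim, and align the Abstract wording. State that the regression step yields overall associations.

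The cost is rewording and a little more analysis. The data and software are unchanged.
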